#### **7.2.2 Serious adverse events (SAEs)**

A serious adverse event is any untoward medical occurrence or effect that

- results in death;
- is life threatening (at the time of the event);
- requires hospitalization or prolongation of existing inpatients' hospitalization of more than one day;
- results in persistent or significant disability or incapacity;
- is a congenital anomaly or birth defect; or
- any other important medical event that did not result in any of the outcomes listed above due to medical or surgical intervention but could have been based upon appropriate judgement by the investigator.

An elective hospital admission will not be considered as a serious adverse event.

The investigator will report all SAEs to the sponsor without undue delay after obtaining knowledge of the events.

### **7.3 Safety reporting**

#### **7.3.1 Adverse events**

Adverse events occurring from the first study-related procedure until 30 days after protocol treatment will be recorded in the CRF.

#### **7.3.2 Follow-up of adverse events**

All adverse events will be followed until they have abated, or until a stable clinical situation has been reached. Depending on the nature of the event, follow up may require additional tests or medical procedures as indicated, and/or referral to the general physician or a medical specialist.

All AEs must be documented and the outcome must be followed-up until the return to normal or consolidation of the patient's condition.

Subjects withdrawn from the study due to any AE will be followed at least until the outcome is determined even if it implies that the follow-up continues after the patient has left the trial.

#### **7.3.3 Reporting Serious Adverse Events**

Serious Adverse Events (SAEs) will be reported from the first study-related procedure until 3 months postpartum.

SAE's must be reported by e-mail to the study project team within 24 hours after the event was reported to the investigator, using the provided SAE report form.

This initial report should minimally contain information with respect to the event, associated treatment and patient identification, as described in the detail in the instructions for the SAE report form. If necessary, more detailed information should be provided in a follow-up report within a further 2 business days. SAE's need to be reported until end of study as defined in the protocol.

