## **2. OBJECTIVES**

**Primary Objective:** to compare safety and efficacy of POEM and EBD as first-line treatment for achalasia in children based on a superiority design.

**Primary outcome measure:** the need for retreatment (i.e. EBD, LHM, POEM or intra-sphincteric botox injection performed *or* scheduled) due to recurrent or persisting symptoms (Eckardt score > 3) *with* evidence of recurrence on barium swallow *and/or* HRM within 12 months after initial treatment (see page 21 and 22 for further explanation), as assessed by a blinded end-point committee (PROBE design)

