#### 6.1.2 Secondary study parameters/endpoints (if applicable)

Secondary study parameters/outcomes include (see page 26 for follow-up schedule):

- Achalasia symptoms (Eckardt score); Health-related- and disease specific QoL (Pediatric Quality of Life inventory (PedsQL) 4.0, Gastro-intestinal QoL (Pediatric Quality of Life inventory – GI) and Achalasia disease specific QoL questionnaire (DSQoL)) (37-39, 55)

- Reflux symptoms (reflux disease questionnaire, RDQ)
- LA grade (EGD)
- 24 hour pH-impedance (pH-MII) measurement parameters (Table 1)
- HRM parameters (Table 1)
- Procedure times
- Complications (any unwanted events that arise following treatment and/or that are secondary to the treatment)
  - o Severe: resulting in admission >24 hours or prolongation of an already planned admission of >24 hours, admission to a medium or intensive care unit, additional endoscopic procedures, blood transfusion or death.
  - o Mild: all other complications.

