***Peroral endoscopic myotomy (POEM)***

POEM will be performed by experienced (pediatric) endoscopists, who have independently performed over 15 procedures. Patients are admitted two hours prior to the POEM procedure and are scheduled to be discharged within 48 hours post-procedure. Patients are asked to use a diet with clear fluids starting 48 hours before the procedure and nil per mouth starting 8 hours before the procedure. On the day of the procedure, antibiotics and double dose PPI are administered intravenously (see page 28 and 29 for medicament and dosage). The mouth, throat and esophagus are rinsed with saline and chlorhexidine (40–60 ml). POEM procedures are then performed as described by Inoue et al. The endoscopic procedure will be recorded on video to make evaluation afterwards possible. Pictures to evaluate LA grade of GERD will be taken. A forward-viewing upper endoscope is used with a transparent distal cap. Carbon dioxide gas is used for insufflation during the procedures. An endoscopic dissection knife is used to access the submucosa, to create the submucosal tunnel, and also to divide circular muscle fibers over a minimum length of 6 cm in the esophagus, and 2 cm onto the cardia according to the standards of surgical myotomy. An electrogenerator is used with Endocut Q mode (effect 2) to open the mucosa, and spray coagulation mode (effect 2, 50 watt) to dissect the submucosa and divide the muscle fibers. A coagulating forceps is used for hemostasis as needed. Closure of the mucosal entry site is performed using standard endoscopic clips.

Patients are discharged with a soft diet for 2 weeks.

*Reflux surveillance*

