#### **10.5 Temporary halt and (prematurely) end of study report**

The investigator/sponsor will notify the accredited MREC of the end of the study within a period of 8 weeks. The end of the study is defined as the patient's last visit.

The sponsor will notify the MREC immediately of a temporary halt of the study, including the reason of such an action.

In case the study is ended prematurely, the sponsor will notify the accredited MREC within 15 days, including the reasons for the premature termination.

Within one year after the end of the study, the investigator/sponsor will submit a final study report with the results of the study, including any publications/abstracts of the study, to the accredited MREC.

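### SAE reporting ends at a time that does not exist in this trial, and non-serious AEs are recorded for longer after EBD than after POEM; both need one common window.

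*Protocol*

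**What the plan says.** **SAE window.** Section 7.3.3 states that SAEs "will be reported from the first study-related procedure until 3 months postpartum". The section then closes with "SAE's need to be reported until end of study as defined in the protocol". Section 10.5 supplies that definition: "The end of the study is defined as the patient's last visit".

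**AE window.** Section 7.3.1 reads: "Adverse events occurring from the first study-related procedure until 30 days after protocol treatment will be recorded in the CRF". Section 7.2.1 defines an AE by its occurrence at any time in the study and has every reported or observed event recorded. Section 7.4 promises the DSMB a report with all AEs and SAEs of the study. Neither section carries a 30-day limit.

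**Length of treatment.** Under Section 5.1, initial therapy is one procedure for POEM. For EBD it is two sessions two weeks apart, a third session 2-4 weeks after the second if symptoms persist, or, on relapse, a second series of two sessions 2-4 weeks apart. No calendar limit is given for that relapse. Table 2 accepts a second session 1-6 weeks after the first; the EBD text in Section 6.3 gives 10-18 days.

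**Severity.** In Section 6.1.2 one criterion for a severe complication is "resulting in admission >24 hours or prolongation of an already planned admission of >24 hours". POEM patients are "scheduled to be discharged within 48 hours post-procedure". The EBD text in Section 6.3 states no planned stay; only the background in Section 1 mentions that EBD can be an outpatient procedure.

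**Objective.** Section 2 sets out "to compare safety and efficacy of POEM and EBD as first-line treatment for achalasia in children based on a superiority design".

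**The concern.** Safety is named in the primary objective, so the rules for collecting harms should be unambiguous and equal between arms. They fall short in three ways.

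- Sites have a 24-hour reporting duty for SAEs but are given two end points for it, one of which cannot be determined for any participant.
- The AE window is tied to the end of a treatment course that is longer in one arm. Within the EBD arm it also depends on outcome: a child who does badly receives more sessions and is therefore observed for longer.
- Once the window closes, non-serious events need not be entered in the CRF. That leaves out most of the PPI year, the PPI withdrawal and the T=12 investigations (EGD under general anesthesia, catheter placement), for which Section 9.4 itself names possible complications.

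At stake is whether a difference in non-serious AE counts reflects the treatments or the length of observation.

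**Working it through.** The plan gives no length for either window, so there is no figure to reproduce. The sample size concerns retreatment and is not affected.

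**1. SAE window.** Participants are 7 to 17 years old, known pregnancy at treatment is an exclusion (Section 4.3), and no delivery is a trial event. The first end point in Section 7.3.3 therefore has no meaning here. The second has one, through Section 10.5. Both sentences apply to both arms alike.

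**2. AE window.** I take protocol treatment to be the initial therapy of Section 5.1 and count from the first treatment session:

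window (days) = days from first to last protocol session + 30

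| Course | Calculation | Days | Ratio to POEM |
|---|---|---|---|
| POEM | 0 + 30 | 30 | 1.00 |
| EBD, two sessions as scheduled | 14 + 30 | 44 | 1.47 |
| EBD, two sessions, 10-18 days | 10 + 30 to 18 + 30 | 40-48 | 1.33-1.60 |
| EBD, two sessions, Table 2 | 7 + 30 to 42 + 30 | 37-72 | 1.23-2.40 |
| EBD, third session, as scheduled | 14 + 14 + 30 to 14 + 28 + 30 | 58-72 | 1.93-2.40 |
| EBD, third session, Table 2 | 7 + 14 + 30 to 42 + 28 + 30 | 51-100 | 1.70-3.33 |
| EBD, second series from month 6 | 182.4 + 14 + 30 to 182.4 + 28 + 30 | about 226-240 | about 7.5-8.0 |

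Month 6 is taken as 6 × 30.4 = 182.4 days. The last row assumes that recording runs on without a break; the text does not say whether it stops and restarts between series. Section 7.3.1 starts at the first study-related procedure, so any earlier study procedure adds time in both arms. That lowers the ratios but leaves the differences in days.

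**3. What this does to counts.** The protocol gives no background AE rate. Assume a constant rate λ per patient-month, equal in both arms:

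P(at least one recorded AE) = 1 − exp(−λ × days / 30.4)

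| λ (assumed) | POEM, 30 days | EBD, 44 days |
|---|---|---|
| 0.05 | 4.8% | 7.0% |
| 0.10 | 9.4% | 13.5% |
| 0.20 | 17.9% | 25.1% |

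At λ = 0.10 an EBD patient with a third session reaches 17.4-21.1% (58-72 days), or 28.0% at 100 days, and one observed for 240 days reaches 54.6%. With 63 per arm and two sessions for every EBD patient, the expected numbers are 63 × 0.094 = 5.9 (POEM) and 63 × 0.135 = 8.5 (EBD), with no true difference.

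**4. Length-of-stay criterion.** After POEM with a planned stay at the 48 h ceiling, a stay of more than 48 + 24 = 72 h meets it. After EBD without a planned admission, more than 24 h does. The hospitalization item of the SAE definition (Section 7.2.2) is built the same way. The 72 h is an upper bound, and the EBD side rests on background text.

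**The case against.** Much of the safety comparison does not depend on the AE count, and several stronger readings that a reader might infer are not supported.

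- **That SAE capture favors one arm.** It does not. The wording is wrong, but the end-of-study sentence covers both arms equally, and applying it keeps SAEs comparable.
- **That the AE window misses the reflux expected after POEM.** The 41% versus 7% esophagitis in the cited adult trial came from scheduled endoscopy at 12 months. This protocol also schedules EGD and pH-MII at 12 months in all participants, off PPI, with the RDQ at 3, 6 and 12 months. These are named secondary outcomes.
- **That procedure-related complications are cut off at 30 days.** The definition in Section 6.1.2 has no such limit, and its intensive care, transfusion and death criteria do not depend on planned stay.
- **That EBD observation is typically 3.3 times longer.** That needs a third session and both maximum intervals. The scheduled ratio is 1.47.
- **That every extra AE in the EBD arm is an artefact.** Events caused by further dilations are true harms of the EBD strategy. Only background events in the longer window are artefact.
- **That prescribed dilations make a complication severe as additional endoscopic procedures.** The definition requires the procedure to result from a complication; these dilations follow from persisting symptoms or relapse.

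All of this stands. What it leaves untouched is the impossible SAE end point, the conflict of Section 7.3.1 with Sections 7.2.1 and 7.4, and the unequal window for non-serious AEs. Sections 7.2.1 and 7.4 do not repair that window: they contradict it, and a CRF closed at 30 days cannot supply the DSMB with all events of the study.

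**Conclusion.** The concern holds for the two windows as written. The SAE window is an error that contradicts its own section, in both arms alike. The AE window contradicts two other sections and gives EBD 44 days against 30 as scheduled, up to 100 with a third session, and about 226-240 with a second series from month 6. Arm bias through the windows is limited to non-serious AE counts and runs against EBD; the loss of later non-serious events affects both arms. It does not follow that safety as a whole cannot be compared.

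The day counts rest on reading protocol treatment, which is not defined, as the initial therapy of Section 5.1. A reading that included the year of PPI would carry the window to about 13 months in both arms, which is one more reason to define the term. The percentages rest on assumed AE rates and show direction and rough size only.

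The length-of-stay criterion is a secondary point. It makes a severe grade easier to reach after EBD than after POEM if EBD is done without a planned admission, which the procedure text does not settle.

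**What to change.** 1. In Section 7.3.3 delete the postpartum end point. In Sections 7.3.1 and 7.3.3 state one window for AEs and SAEs in both arms: from first study procedure (or randomization) to the T=12 visit or end of study. Bring Sections 7.2.1 and 7.4 into line.
2. Name the origin from which the 12 months run. Sections 2 and 3 count from initial treatment, while the reflux surveillance text in Section 6.3 counts from randomization. Unless this is settled, the length of the EBD course could re-enter the window.
3. Tabulate AEs over equal periods in both arms: 0-30 days after each procedure, and the whole 12 months. The first shows harm per procedure, the second the harm of each strategy over the same time.
4. Report severe complications also without the length-of-stay criterion. A single clock of total hours in hospital is not a good substitute, because it could grade a trivial event within a routine POEM stay as severe.

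The cost is a change of wording, a little extra AE entry at the existing 3, 6 and 12 month visits, and one additional table. Sample size and visit schedule stay as they are.

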#### **7.3.4 Follow-up of Serious Adverse Events**

All serious adverse events will be followed clinically until they are resolved or until a stable situation has been reached. Depending on the event, follow up may require additional tests or medical procedures as indicated and/or referral to a general physician or a medical specialist.

Follow-up information on SAEs should be reported monthly until recovery or until a stable clinical situation has been reached. The final outcome of the SAE should be reported on a final SAE report.

#### **7.3.5 Processing of Serious Adverse Events**

During the course of the study, the sponsor will report in an expedited manner to the Health Authorities, the Ethic Committees in each country in accordance with international and local regulations.

SAE's that result in death or are life threatening should be reported immediately with a maximal 7 days for a preliminary report with another 8 days for completion of the report. All other SAEs will be reported within a period of maximum 15 days after the sponsor initially received knowledge of the serious adverse events.

If required by national laws or regulations or by the procedures of the authorities, the sponsor will ensure that a six-monthly line listing of all reported SAEs is submitted to the Ethics Committee(s).

#### **7.3.6 Reporting of Safety Issues**

The sponsor will promptly notify all concerned investigators, the Ethics Committee(s), and regulatory authorities of findings that could affect adversely patient safety, have impact on the execution of the trial, increase the risk of participation or otherwise alter the EC's approval to continue the trial.

In the occurrence of such an event the sponsor and the investigators will take appropriate urgent safety measures to protect the patients against any immediate hazard. Pending further review, the accredited Ethics Committee will suspend the study, except insofar as suspension would jeopardize patient's health. The local investigator will inform patients participating in the trial.

#### **7.4 Data Safety Monitoring Board (DSMB)**

A Data Safety Monitoring Board (DSMB) is established. In total the DSMB will consist of three members, an epidemiologist, a pediatric gastroenterologist and a gastroenterologist. None of the members have a conflict of interest with the sponsor of the study. Personal details of the DSMB members can be found in the DSMB charter which also describes in detail the function, aims and responsibilities of the DSMB. In short the DSMB will act in an independent, expert and advisory capacity to monitor participant safety. The DSMB will evaluate safety of participants after 50 participants have reached 1 year follow up. At this time, the DSMB will be provided with an interim analysis report including outcome measures and all adverse events and serious adverse events that occur during the study.

The advice(s) of the DSMB will only be sent to the sponsor of the study. Should the sponsor decide not to fully implement the advice of the DSMB, the sponsor will send the advice to the reviewing MREC, including a note to substantiate why (part of) the advice of the DSMB will not be followed.

## **8 STATISTICAL ANALYSIS**

All normally distributed data will be presented as means and standard deviations (SD). Data where normal distribution cannot be assumed, will be reported as median and range.

The success rate of the two procedures and their odds ratio will be analysed using logistic regression with adjustment for stratification factors. Superiority of POEM is shown when the primary outcome (need for retreatment) is significantly lower in the POEM treatment arm (defined as  $p < 0.05$ ). Data will be shown in point estimates and 95% confidence intervals.

Comparisons between groups will be made using multiple linear regression analysis for continuous data, if necessary after (log)transformation and multiple logistic regression analysis for categorical data for secondary outcomes, adjusting for stratification factors.

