#### **4.4 Sample size calculation**

A recent retrospective review of 21 pediatric achalasia patients, of which 12 received POEM and 9 EBD, reported treatment success (Eckardt score  $\leq$  3) at 12, 24 and 36 months follow-up to be 100% for POEM at all follow up moments and 66.7% vs 44.4% vs 33.3% at 12, 24 and 36 months follow-up for EBD patients respectively.(16) However, in this study no repeated EBD-treatment was allowed in case of clinical recurrence. In adults 76% of patients treated according to our protocol had clinical success after 12 months.(54) Age is known to be a factor in predicting

success-rates of EBD with worse outcome in younger patients.

Taken all this together, we assumed a success rates of 72.5% for EBD and 92.5% for POEM in children after one year, we estimated that with 56 patients in each group, the study would have 80% power to detect a significant difference in success rate between EBD and POEM with a two-sided alpha level of 0.05. To cope with an estimated 10% loss to follow-up, we aim to enroll a total number of 126 patients (63 patients in each group). It is assumed that patient enrollment will be accomplished within 5 years, after approval from all local institutional review boards (IRBs).

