## **6.2 Randomization, blinding and treatment allocation**

When participants are recruited for the study, the time to consider participation is up to four weeks. Before randomization, the patient (if  $\geq 12$  years) and all legal guardians (if patients <16 years) must have signed the informed consent form.

Randomization will be performed by using a web-based program (Castor electronic data capture (EDC) system) and will be stratified per center, to reach equal number of patients treated with POEM or EBD in each center. To ensure balance of treatment groups, stratified block randomization with randomly selected block sizes in order to minimize selection bias will additionally be performed within each center. Castor EDC will generate the allocation sequence. Allocation concealment is applied to all investigators, clinicians and patients. One blinded central reader will analyze all HRM and pH-MII measurements and a second blinded central reader will analyze all barium esophagrams.

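### With about 20 expected failures, ordinary centre-adjusted logistic regression exaggerates the odds ratio, and it gives no finite odds ratio if POEM has no failures

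*Protocol*

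**What the plan says.** Section 8 sets the primary analysis: "The success rate of the two procedures and their odds ratio will be analysed using logistic regression with adjustment for stratification factors". The decision rule follows: "Superiority of POEM is shown when the primary outcome (need for retreatment) is significantly lower in the POEM treatment arm", at p < 0.05. It also sets what is reported: "Data will be shown in point estimates and 95% confidence intervals".

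Section 6.2 makes centre the stratification factor: randomization "will be stratified per center, to reach equal number of patients treated with POEM or EBD in each center". No other factor is named, and the number of centres is not given.

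Section 4.4 sizes the trial: "we assumed a success rates of 72.5% for EBD and 92.5% for POEM in children after one year", and "we estimated that with 56 patients in each group, the study would have 80% power to detect a significant difference in success rate", "with a two-sided alpha level of 0.05". Enrolment is raised to 63 per arm for 10% loss.

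Section 8 does not say how the model is estimated, whether centre enters as fixed or random, which test gives the p-value, or what happens if one arm has no events.

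**The concern.** Maximum-likelihood logistic regression is biased away from the null when events are few relative to the parameters. With one term per centre, centres where every patient has the same outcome contribute nothing to the treatment effect, and the estimate drifts further from 1 as centres multiply. If one arm has no events, the likelihood has no finite maximum for the odds ratio.

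The planning rates put this trial where both problems can arise. At stake are an exaggerated headline effect, some loss of type I error control if there are many centres, and a small but real chance that the stated output (an odds ratio with a 95% confidence interval) cannot be produced just when POEM does best.

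**Working it through.** **1. The plan's own figure.** Failure rates from section 4.4 are 27.5% (EBD) and 7.5% (POEM), mean 17.5%. The pooled two-proportion formula without continuity correction is n = (A + B)² ÷ d², with

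- A = 1.96 × √(2 × 0.175 × 0.825) = 1.053
- B = 0.8416 × √(v₁ + v₂) = 0.436, where v₁ = 0.275 × 0.725 = 0.1994 and v₂ = 0.075 × 0.925 = 0.0694
- d = 0.20

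This gives n = 55.5, so 56 per arm, with power 0.804. Then 56 ÷ 0.9 = 62.2, so 63 per arm and 126 in total. The stated sample size is reproduced.

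**2. Events and true odds ratio.**
- At 56 per arm: 56 × 0.275 = 15.4 EBD failures and 56 × 0.075 = 4.2 POEM failures, 19.6 in total.
- At 63 per arm: 17.3 and 4.7, 22.1 in total before rounding.
- Odds of failure: 0.075 ÷ 0.925 = 0.0811 for POEM and 0.275 ÷ 0.725 = 0.379 for EBD, so the odds ratio, POEM vs EBD, is 0.214.

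**3. Ordinary centre-adjusted fit.** Trials were simulated at 56 per arm with blocked 1:1 allocation within centre and centre as fixed effects (3,000 to 6,000 trials per scenario, Monte Carlo standard error about 0.3 to 0.4 points at 5%). The centre counts are assumptions. Type I error was taken at 17.5% failure in both arms.

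| Centres | Median odds ratio (true 0.214) | Type I, Wald | Type I, likelihood ratio |
|---|---|---|---|
| 3 | 0.201 | 4.3% | 5.2% |
| 6 | 0.190 | 4.7% | 5.8% |
| 10 | 0.181 | 5.7% | 6.8% |
| 15 | 0.166 | 6.0% | 7.0% |
| 20 | 0.150 | 6.5% | 7.8% |

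Mean bias of the log odds ratio runs from 7% (3 centres) to 27% (20). Ten unequal centres with between-centre SD 0.5 on the logit scale gave similar results: median 0.182, type I error 5.9% and 7.1%. At 63 per arm, type I error (Wald / likelihood ratio) was 4.7% / 5.6% with 5 centres and 5.4% / 6.0% with 10.

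To translate the bias: with EBD failure at 27.5% (odds 0.379), an odds ratio of 0.181 implies POEM odds of 0.0687, a failure rate of 6.4%, and 0.150 implies odds of 0.0569, a rate of 5.4%, against the true 7.5%.

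**4. No POEM failures.** The probability is (1 − p)^56. For p = 7.5% it is 1.3% (0.7% at 63 per arm). Exact enumeration at 56 per arm, EBD 27.5%, no centre terms:

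| POEM failure rate | P(no failures) | Wald power | Chi-square power |
|---|---|---|---|
| 7.5% | 1.3% | 79.2% | 82.7% |
| 5% | 5.7% | 86.0% | 93.1% |
| 3% | 18% | 78.8% | 97.9% |
| 2% | 32% | 66.3% | 99.2% |

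Wald power falls at the lowest POEM failure rates. For 0/56 vs 15/56, the fit diverges (log odds ratio about −31, standard error about 10⁶, Wald p = 1.0). The likelihood-ratio test gives χ² = 23.1, p = 1.5×10⁻⁶, and Fisher's test p = 2×10⁻⁵.

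**5. Alternatives, same setting, at 3, 10 and 20 centres in that order.**
- Firth-penalised logistic regression with centre, penalised-likelihood test: type I error 5.0%, 4.6% and 4.8%; median odds ratio 0.224 at 3 centres, 0.230 at 10 and 0.238 at 20; power 82%, 81% and 80%.
- Centre-stratified Cochran-Mantel-Haenszel test: type I error 5.2%, 4.8% and 5.5%; power about 82%.
- For 0/56 vs 15/56 without centre terms, Firth is equivalent to adding 0.5 to each cell: the odds are 0.5 ÷ 56.5 = 0.00885 and 15.5 ÷ 41.5 = 0.373, so the odds ratio is 0.024, which is finite.

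**The case against.** The best reply is that section 8 names neither maximum likelihood, fixed centre effects nor a Wald test. Firth and random-intercept models are also logistic regression adjusted for centre, and such detail commonly sits in a statistical analysis plan, which is not shown. This is fair, and silence on these details is not the finding. But the stated method has an ordinary reading, and that reading fits the protocol's own event count poorly.

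Three stronger readings are tempting, and the document does not support them.

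- *A reader might infer that type I error is inflated whatever the design.* It is not. It is nominal or within about a point at 3–6 centres, and the number of centres is unknown. The cited incidence (0.1–0.18 per 100,000 children per year) and 126 children in 5 years (25.2 a year) imply a base of 25.2/0.0000018 = 14 million to 25.2/0.000001 = 25 million children, even if every case enrolled. That makes many centres plausible but does not establish it. Section 6.1.1 also carries the last available data of lost patients into the intention-to-treat analysis, so the analysed number may be nearer 126, which eases the problem slightly.
- *A reader might take the 100% POEM success in section 4.4 as predicting no failures.* That result is 0 of 12 in one retrospective study (exact 95% upper limit 26%), on Eckardt score rather than retreatment. Section 1 also cites 93% success at one year in 44 children, and section 4.4 itself assumes 92.5%.
- *A reader might conclude that superiority could not be shown at all with no POEM failures.* That holds for the Wald test only. The likelihood-ratio test still rejects, and the success rates by arm remain reportable.

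Sizing on two proportions and analysing by logistic regression is ordinary practice. At the planning rates the unadjusted Wald power of 79.2% is immaterially below 80%.

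**Conclusion.** The point holds in a limited form. Under ordinary fixed-effect fitting, the centre-adjusted odds ratio was exaggerated at every number of centres examined: slightly at 3 (0.20 against 0.214), clearly at 10 (0.18–0.19) and substantially at 20 (0.15). The effect on type I error is secondary and appears only from about 10 centres up. Failure to produce an odds ratio is a tail risk of about 1% on the planning assumptions, and matters (18–32%) only if the true POEM failure rate is 3% or 2%.

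This rests on maximum-likelihood estimation with fixed centre terms, the failure rates in section 4.4, and assumed centre counts of 3 to 20. If there are only a few centres, the remaining problem is small.

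**What to change.** In section 8, name Firth-penalised logistic regression adjusted for centre as the primary analysis, with a penalised-likelihood test and profile-likelihood 95% confidence interval. Alternatively, take the p-value from a centre-stratified Cochran-Mantel-Haenszel test and the odds ratio from the penalised model. Pool small centres by a rule fixed before database lock. The odds ratio can stay the primary measure; report the difference in success rates with its 95% confidence interval alongside. Making the risk difference primary would be a preference, not a correction.

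The cost is a few sentences, a little more analysis work and slight shrinkage of the odds ratio toward 1 (median 0.224–0.238 against 0.214). No extra patients are needed: power stays at about 80–82% with 56 per arm.
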